**Methods:**

A cross-sectional study of 1008 young adults will be conducted. Individuals are eligible to participate if they: (1) are aged between 18 and 30 years; (2) reside in New South Wales, Australia; (3) own or have access to a smartphone; (4) are English-literate; and (5) consume at least one meal, snack, or drink purchased outside the home per week. An even spread of gender, age groups (18 to 24 years and 25 to 30 years), metropolitan or regional geographical areas, and high and low socioeconomic status areas will be included. Participants will record all food and drink consumed over 3 consecutive days, together with location purchased and consumed in our customized smartphone app named Eat and Track (EaT). Participants will then complete an extensive demographics questionnaire. Mean intakes of energy, nutrients, and food groups will be calculated along with the relative contribution of foods purchased and eaten away from home. A subsample of 19.84% (200/1008) of the participants will complete three 24-hour recall interviews to compare with the data collected using EaT. Data mining techniques such as clustering, decision trees, neural networks, and support vector machines will be used to build predictive models and identify important patterns.

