### Knowledge Gaps

Although foods purchased and eaten away from home can impact nutritional status [13,21], the most recent Australian National Nutrition and Physical Activity Survey did not collect data on the source of the food and beverages consumed [22]. Limited research has focused on specific food types that may or may not have been sourced outside the home [23] or on determinants of fast food intake [8,24]. Only one Australian study has been conducted on the consumption of foods purchased outside of home and how this affects the total diet [25]. However, that analysis was conducted using data collected more than 20 years ago, and as Australians’ expenditure on fast foods and eating out has been increasing [9], as have the rates of overweight and obesity, it is timely to revisit the role of eating out on diet quality and risk factors for chronic disease. The exact quantities, type, and frequency of consumption of food prepared outside home by young adults and the impact this has on their energy, macronutrient, and micronutrient intakes is currently unknown. To address these gaps in knowledge, the proposed project will collect data on the frequency, type, amount, and place of purchase of foods prepared away from home, together with sociodemographic data in a population sample of 18- to 30-year-old Australians.

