## Methods

### Aims

The study will determine how frequently young adults purchase and consume foods away from home in the context of their entire diet, and what types of foods they are purchasing and consuming. The relative contributions of different food outlets (eg, fast food chain, independent takeaway food store, coffee shop, restaurant, cafeteria) to overall food and beverage intake of young adults will be established. Finally, the extent to which food and beverages consumed away from home contribute to the total energy and nutrient intake of young adults will be determined using the complete 3-day food and beverage intake data records.

As a substudy, the comparative validity of data collected by the app will be determined using the 24-hour recalls.

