Once participants have recorded the foods and drinks they consumed, they then enter the amounts ingested into the EaT app (Figure 3), together with the location from which the food was sourced (Textbox 2). Participants were instructed to choose “home” for all foods not purchased and consumed outside the home. While not mandatory, participants are encouraged to weigh and measure the foods and drinks before consumption, and there is a check button to indicate if foods have been weighed. If not weighed, participants are encouraged to use the Food Model booklet to estimate their amounts in household measures, or they can enter a default portion size. These default sizes are based on typically consumed portion sizes for males and females aged 18 to 30 years based on the latest national dietary survey [41]. If participants cannot find a food listed in the app’s database, they will be able to manually enter it as a new food, and this will be flagged to the research team for follow-up. Each entry is time and date stamped, and thereby indicates whether all entries are made at one time or recorded prospectively throughout the day.

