**Figure 3 figure3:**
[figure not shown]
Eat and Track (EaT) app screenshots showing the landing screen, food logging screen, and pink button filtering of foods.

Locations for food source included in the Eat and Track App.Fast food chain (Chain outlets selling takeaway foods, such as burgers, pizza, or fried chicken)McDonald’s, KFC, Pizza Hut, Mad MexCoffee chain (Chain outlets selling predominantly coffee and tea)Gloria Jean’s Coffee, StarbucksCold drink chain (Chain outlets selling predominantly cold drinks, including juice, smoothies, or iced tea)Boost Juice, EasyWay TeaIce creamery/frozen yogurt (Chain or independent outlets selling predominantly ice cream, gelato, or frozen yogurt)New Zealand Natural, Yogurberry, local ice creameryOther takeaway (Independent outlets selling any type of takeaway foods)Local fish and chip shop, local pizzeriaIndependent café or restaurant (Independent sit-down café or restaurant selling any type of cuisine; may also do takeaway food)Asian/Indian restaurant, local café, other restaurantsBakery or patisserie (Chain or independent outlets selling predominantly baked goods, such as cakes, breads, and sweets)Michel’s Patisserie, Muffin Break, local bakeryService station/convenience store (Food bought from service stations or convenience stores, including cafes in these locations)7-Eleven, Wild Bean Café, or BP, Shell or Mobil service stationsPub or club (Restaurants, bars, cafes or bistros in pubs or clubs)Bowling, RSL, sports or community clubs, local hotelsHome (Any food not sourced from the locations above.)Includes homemade food, food prepared by friends or relatives, or foods purchased from supermarkets

At the conclusion of each day’s recording, participants will complete a short survey. This survey will determine whether the day’s food and beverage intake, frequency of eating away from home, physical activity, stress, and sleep levels were higher or lower than usual. Additionally, self-reported healthiness of the day’s dietary intake, assessed by a 5-point Likert scale, ranging from “very unhealthy” to “very healthy” was included in the end of day survey.

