#### Consumption of Foods Purchased and Eaten Away From Home

The average frequency of meals, drinks, and snacks (collectively, and by occasion) purchased and eaten away from home will be calculated. Multivariate regression models will be used to determine the health, social, and environmental factors associated with consumption of foods purchased and eaten away from home. The relative contribution of foods purchased and eaten away from home to total energy and macronutrient intake will be calculated.

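### The participant instruction for 'home' and the app's source list sort takeaway eaten at home in opposite ways, so food source may be coded inconsistently

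*Protocol article*

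**What the plan says.** The section on the Eat and Track app says that participants enter the amount of each food, "together with the location from which the food was sourced (Textbox 2". It then adds: "Participants were instructed to choose “home” for all foods not purchased and consumed outside the home".

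Textbox 2 lists the choices. Each outlet category, including fast food chains and other takeaway, is defined by the type of outlet, with no condition on where the food is eaten. 'Home' is the residual category for food that came from none of the listed outlets. Its note reads: "Includes homemade food, food prepared by friends or relatives, or foods purchased from supermarkets".

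The abstract describes the record more broadly: food and drink are logged "together with location purchased and consumed in our customized smartphone app named Eat and Track (EaT".

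The quantity to be measured is worded in three ways:
- Knowledge Gaps: "frequency, type, amount, and place of purchase of foods prepared away from home".
- Aims: "The relative contributions of different food outlets (eg, fast food chain, independent takeaway food store, coffee shop, restaurant, cafeteria) to overall food and beverage intake".
- Statistical analysis: "The relative contribution of foods purchased and eaten away from home to total energy and macronutrient intake will be calculated".

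**The concern.** The instruction attaches two conditions to choosing an outlet, purchase and consumption outside the home. The list attaches one, the source. The item on which they part is takeaway or delivered food eaten at home, which is a central item for a study that names the independent takeaway store among the outlets to be quantified.

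The source field feeds the outlet contributions in the Aims, the frequency and energy-share results in the section on foods eaten away from home, and the regression models there. The Conclusions also rest the estimate of how often young adults eat out on it. An entry logged as 'home' loses its outlet. If some participants follow the instruction and others the list, the same meal is coded in two ways.

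No described check is aimed at this. Data Cleaning names free-text items, gross entry errors and skipped meals. The validation substudy compares energy, nutrients and food groups, not source labels.

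**Working it through.** The article states no figure for this variable, so there is none to reproduce. The check is a comparison of the two rules, followed by an illustration on assumed inputs.

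**1. The two rules side by side**

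| Food | Instruction, plain reading | Textbox 2 |
|---|---|---|
| Outlet food eaten out | outlet | outlet |
| Outlet food eaten at home | home | outlet |
| Supermarket food eaten at home | home | home |
| Supermarket food eaten out | not home | home |
| Homemade food eaten out | home | home |

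The rules disagree on the second and fourth rows, in opposite directions. For the fourth row the instruction also leaves the participant without a fitting category, because the list has no supermarket entry outside 'home'.

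**2. Which measure each rule serves, for outlet food eaten at home**

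- Outlet contribution (Aims) and food prepared away from home (Knowledge Gaps): the list is right. The instruction leaves this food out, so the measure is too low.
- Food both purchased and eaten away (statistical analysis, read literally): the instruction is right. The list counts this food in, so the measure is too high.

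A single source field cannot serve both measures unless place of eating is also known.

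**3. Illustration of size**

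Inputs, none given in the documents:
- S = true share of energy obtained from outlets, assumed 20%, 30% or 40%.
- h = part of S eaten at home, assumed 0% to 50%.

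If everyone follows the instruction, recorded outlet share = S × (1 − h), and the loss is S × h.

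| S | h = 0% | h = 10% | h = 25% | h = 50% |
|---|---|---|---|---|
| 20% | 20% | 18% | 15% | 10% |
| 30% | 30% | 27% | 22.5% | 15% |
| 40% | 40% | 36% | 30% | 20% |

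For S = 30% the loss is 0, 3, 7.5 and 15 points.

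If everyone follows the list, the outlet share is recorded as S without loss. The bought-and-eaten-away share, truly S × (1 − h), is then also recorded as S. It is too high by the same S × h.

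**4. Mixed behaviour**

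If a fraction c of this food is logged by the instruction, recorded outlet share = S × (1 − h × c). With S = 30% and c = 0.5:
- h = 10%: 30% × (1 − 0.05) = 28.5%, a loss of 1.5 points.
- h = 50%: 30% × (1 − 0.25) = 22.5%, a loss of 7.5 points.

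**5. The opposite shift**

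Let g be the share of energy from supermarket food eaten out and logged to an outlet under the literal instruction. Recorded outlet share = S × (1 − h) + g, so the net error is g − S × h. With S = 30% and h = 25%, it is zero at g = 7.5 points. The documents give neither g nor h, so they do not fix the net direction.

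**The case against.** The strongest reply is that the sentence is a one-line summary of what participants were told. The user guide, videos and three tutorial screens are not shown. The sentence just before it speaks of where the food was sourced, participants choose from a list whose definitions point to the outlet, and the Conclusions again describe the requirement as recording source. The article uses its various eating-out phrases loosely throughout, so the instruction may have been meant and understood as 'not bought out'. This stands: the documents do not show which rule prevailed, and inconsistent coding is a possibility, not an established fact.

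Three stronger readings are tempting and are not supported.

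- A reader might infer that place of eating is not recorded and that the two kinds of food can never be separated. The app section and Textbox 2 describe only a source field, but the abstract says location consumed is recorded, and the app screenshots are not available here. This is a discrepancy to resolve, not a proven gap.
- A reader might infer a downward bias in every main result. The article names no primary measure, total energy, nutrient and food-group intakes do not use the field, 'home' is correct for the literal bought-and-eaten-away measure, and supermarket food eaten out pulls the other way.
- A reader might set the illustrated losses against the stated ±3% margin of error. That margin is for proportions estimated from 1008 participants. A share of energy is a mean of a continuous quantity, whose precision the article does not state, so the comparison is not valid.

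What the reply does not remove is that two stated rules conflict on their plain wording. That is not detail left out by a condensed article.

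**Conclusion.** The instruction and the source list conflict for outlet food eaten at home and, in the opposite direction, for supermarket food eaten out. Such items may be coded inconsistently. For takeaway, following the instruction literally understates outlet contributions and intake of food prepared away from home; following the list overstates the bought-and-eaten-away measure. One of the planned measures is therefore at risk under either rule unless place of eating is recorded.

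The size cannot be determined from the documents. With the assumed 30% outlet share and 0% to 50% of it eaten at home, full adherence to the instruction would record 30% down to 15%; at the lower end of h there is no loss at all. These figures leave out supermarket food eaten out. Actual misclassification and its net direction are not shown.

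It is worth settling promptly: the instruction is reported in the past tense and recruitment is underway, so ambiguous records may already be accumulating.

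**What to change.** 1. Reword the instruction, user guide, videos and tutorial screens so that the source field always means the outlet where the item was obtained, wherever it is eaten, as in Textbox 2. Supermarket food then stays under 'home' even when eaten out.
2. Confirm that place of consumption is recorded separately, as the abstract says, and describe the field in the app section. If it is not recorded, add a yes/no item asking whether the food was eaten at home.
3. Define and report two measures: food purchased away, and food purchased and eaten away. State which one each aim and regression model uses.
4. For existing records, list entries that carry one of the 2229 fast food menu items but are labelled 'home'. Query those still within the two-day checking window and flag the rest. Run a sensitivity analysis that recodes them to the outlet. This cannot recover independent takeaways, so it addresses only part of the problem.

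Cost: revised wording, possibly one tick-box in the app, and some checking of existing records. The downside is slightly more participant burden and two versions of the instrument. A version flag is therefore needed in the main analysis and, because the app is the tool being validated, in the substudy as well.

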**Figure 3 figure3:**
[figure not shown]
Eat and Track (EaT) app screenshots showing the landing screen, food logging screen, and pink button filtering of foods.

Locations for food source included in the Eat and Track App.Fast food chain (Chain outlets selling takeaway foods, such as burgers, pizza, or fried chicken)McDonald’s, KFC, Pizza Hut, Mad MexCoffee chain (Chain outlets selling predominantly coffee and tea)Gloria Jean’s Coffee, StarbucksCold drink chain (Chain outlets selling predominantly cold drinks, including juice, smoothies, or iced tea)Boost Juice, EasyWay TeaIce creamery/frozen yogurt (Chain or independent outlets selling predominantly ice cream, gelato, or frozen yogurt)New Zealand Natural, Yogurberry, local ice creameryOther takeaway (Independent outlets selling any type of takeaway foods)Local fish and chip shop, local pizzeriaIndependent café or restaurant (Independent sit-down café or restaurant selling any type of cuisine; may also do takeaway food)Asian/Indian restaurant, local café, other restaurantsBakery or patisserie (Chain or independent outlets selling predominantly baked goods, such as cakes, breads, and sweets)Michel’s Patisserie, Muffin Break, local bakeryService station/convenience store (Food bought from service stations or convenience stores, including cafes in these locations)7-Eleven, Wild Bean Café, or BP, Shell or Mobil service stationsPub or club (Restaurants, bars, cafes or bistros in pubs or clubs)Bowling, RSL, sports or community clubs, local hotelsHome (Any food not sourced from the locations above.)Includes homemade food, food prepared by friends or relatives, or foods purchased from supermarkets

At the conclusion of each day’s recording, participants will complete a short survey. This survey will determine whether the day’s food and beverage intake, frequency of eating away from home, physical activity, stress, and sleep levels were higher or lower than usual. Additionally, self-reported healthiness of the day’s dietary intake, assessed by a 5-point Likert scale, ranging from “very unhealthy” to “very healthy” was included in the end of day survey.

Data will be collected on 3 consecutive days, and across the entire sample the start days will be spread to capture data for an equal number of weekdays and weekends. In total, data will be collected for 3024 days, including 1512 weekdays (considered Monday to Thursday) and 1512 weekends (Friday to Sunday) to allow for differences between weekdays and weekends to be investigated. Fridays were considered weekend days as previous research has shown that eating habits on Fridays are more like Saturdays and Sundays than weekdays [42].

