**Conclusions:**

The contribution of foods prepared away from home, in terms of energy, nutrients, deleterious nutrients, and food groups to young people’s diets will be determined, as will the impact on meeting national recommendations. Foods and consumption behaviors that should be targeted in future health promotion efforts for young adults will be identified.

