### Screening and Consent

The screening survey (Textbox 1) will be administered at recruitment to collect basic demographic data and consent using the Web-based REDCap research management system [33]. The REDCap system will be programmed to screen participant demographics to fill the study’s demographic quotas. The REDCap system also allows stratified randomization in the substudy (refer to section below).

After completion of the screening questionnaire and enrollment, participants will be notified of their dietary data collection dates, and emailed instructions on how to download and sign up to use the Eat and Track (EaT) app, and obtain a user guide for the EaT app and a copy of the Australian Bureau of Statistics Food Model booklet [34] to assist with estimating portion sizes. Links to useful information on the study website will also be available, including an electronic version of the Food Model booklet.

The study website (Figure 2) was developed to provide information for those participating in this study and future participants. It contains information about the study, its funding and partners, links to the screening questionnaire, technical guides and videos for participants, and links to the Food Model booklet. Potential participants can also contact the study team via email through the website.

Participants will be taught how to use the app using instructional videos and will have access to these videos at all times throughout the study via the study website. Additionally, participants will need to view 3 tutorial screens in the app before they can start recording their intake. They will then record all food and drinks for 3 consecutive days.

Screening questionnaire.Demographics:AgeGenderAboriginality and ethnicityLanguage spoken at homeEducation attainmentPostal code of home addressLiving arrangementRelationship statusEmployment and studyIncomeScreening questions:Do you own a working smartphone?On average, do you have at least one drink, snack or meal you buy away from home each week?(Females only) To your knowledge, are you pregnant and/or breastfeeding?Have you ever been diagnosed or treated for (choose all that apply)?Anorexia Nervosa (screen out)Bulimia Nervosa (screen out)Other eating disorder (screen out)Mental illnessIllicit drug useDiabetesNone of these

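### All supermarket food is coded as Home, so ready-to-eat supermarket items eaten out are missed and the away-from-home share is under-counted by an unknown amount

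*Protocol article*

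**What the plan says.** The Abstract's Conclusions promise that "The contribution of foods prepared away from home, in terms of energy, nutrients, deleterious nutrients, and food groups to young people’s diets will be determined". The Knowledge Gaps section says that the project will "collect data on the frequency, type, amount, and place of purchase of foods prepared away from home". The statistical section on away-from-home consumption words the outcome differently. It analyses food that is both bought and eaten out, and the share of total energy and macronutrients that this food supplies.

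Participants record source in the app from the pick-list in Textbox 2, which has nine outlet types plus Home. Home is the residual code, and its note reads "Includes homemade food, food prepared by friends or relatives, or foods purchased from supermarkets". No exception is made for ready-to-eat items. The service station and convenience store code covers "Food bought from service stations or convenience stores, including cafes in these locations", with no exception for groceries or packaged goods.

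The section on the Eat and Track app gives a second rule, which turns on where food is eaten as well as where it is bought: "Participants were instructed to choose “home” for all foods not purchased and consumed outside the home".

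**The concern.** The outcome is described in terms of preparation, or of buying and eating out, but the code records the type of shop. The gap is widest for supermarkets. A sandwich or hot item bought there and eaten at work was prepared away, bought away and eaten away, yet it carries the same code as a meal cooked at home.

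The away-from-home share is a central result of the study. The consumption it describes is also the outcome of the regression models in the same statistical section and an input to the diet-quality prediction models under Data Mining. If ready-to-eat supermarket food is missed, the published share is too low for the quantity named, and the paper would claim more than the instrument measures. If the two source rules lead participants to code the same item differently, the variable also loses a fixed meaning.

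**Working it through.** **The plan's own figure.** The only precision figure is the margin of error of ±3% for 1008 participants (Population Sampling). With p = 0.5, 1.96 × √(0.5 × 0.5 / 1008) = 0.0309, or 3.1 points, so it reproduces on rounding. It refers to proportions of participants, not to shares of energy. The point here does not depend on it.

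**Classification check.** The table sets each wording against typical items. The items are my examples; the rules are the article's.

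| Item | Prepared away (Abstract, Knowledge Gaps) | Bought and eaten away (statistical section) | Instruction to participants | Textbox 2 |
|---|---|---|---|---|
| A. Ready-to-eat supermarket item, eaten out | away | away | not Home | Home |
| B. Same item, eaten at home | away | not away | Home | Home |
| C. Takeaway from a listed outlet, eaten at home | away | not away | Home | outlet |
| D. Milk or loaf from a convenience store or bakery, used at home | not away, if the term means food-service food | not away | Home | outlet |
| E. Packaged snack from a convenience store, eaten out | depends on reading | away | not Home | outlet |

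1. Row A is away under both outcome wordings and Home in Textbox 2. This is the firm part of the finding.
2. Row B is missed only under the prepared-away wording.
3. The instruction and Textbox 2 disagree in rows A, C and D. In row A the instruction excludes Home, but supermarkets have no other code.
4. Rows D and E carry their own outlet codes, so they can be separated at analysis. Row A cannot. Data Cleaning describes follow-up of free-text entries, gross errors, skipped meals and recipes, but no recoding of source. The Abstract says that the place of eating is recorded too, but a Home-coded item eaten at work could be a packed lunch or a supermarket purchase.

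**Direction and size.** Let u be the share of energy from supermarket food that belongs in the outcome but is coded Home. Let o be the share from outlet-coded groceries or packaged food that does not belong.

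Observed share = true share − u + o, so bias = o − u.

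The documents give neither u nor o. On assumed values only:

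- u = 2%, 5% or 10% with o = 0 gives a bias of −2, −5 or −10 points.
- u from 0 to 10% and o from 0 to 5% gives a net bias from −10 (u = 10, o = 0) to +5 (u = 0, o = 5).
- u = o = 5% gives a net bias of 0, with 10% of energy miscoded.

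Neither term depends on n. Recoding by food code can remove o; what is left is −u.

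**The case against.** The best defence is that the study is about outlets. The objectives and aims ask what different food outlets contribute, and even Knowledge Gaps asks for the place of purchase. Treating supermarkets as home supply is a disclosed and defensible convention for that question. This stands, and it is why the fix is mainly to name the outcome correctly. It does not rescue row A, which is miscoded under the statistical section's own wording as well.

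A reader might infer that the share is misclassified equally in both directions, because convenience-store or bakery groceries used at home count as outlet food. The documents do not support that. The instruction sends such groceries to Home, the over-count needs a food-service reading of prepared away, and those outlets can be split or dropped at analysis.

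A reader might also point to the screening question, "On average, do you have at least one drink, snack or meal you buy away from home each week", and argue that someone who qualifies through supermarket purchases could then score as eating only Home food. That shows no misclassification. Eligibility refers to one item a week and recording covers three days, so an eligible participant may record only Home food under any coding.

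Finally, recruitment is underway. Splitting Home now would put two versions of the source variable in one sample. That is a fair objection to making the split mandatory.

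**Conclusion.** The concern holds in a limited form. Ready-to-eat supermarket food bought and eaten out is coded Home, which lowers the away-from-home share under both outcome wordings, and the source variable cannot undo this. The size is unknown: the 0 to 10% range for u is an assumption for scale, not an estimate.

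The conflict between the instruction and Textbox 2 is a separate fault. Its effect on the share depends on which rule participants follow and which outcome wording is used, so the net direction of all errors together is not established. It would also go too far to say that contrasts by area or socioeconomic status merely reflect shop type. That could happen if shop use differs between these groups, but the article gives no data on it.

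The plan should be changed, because the remedy is cheap and alters what the study can claim. No sample-size or precision figure is affected.

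**What to change.** 1. Adopt one source rule and reconcile the Abstract's Conclusions, Knowledge Gaps, the instruction to participants, Textbox 2 and the statistical section on away-from-home consumption. State whether outlet food eaten at home counts.
2. Report the main result as the share of intake purchased from the listed outlets, and state beside it that ready-to-eat supermarket food is counted as Home.
3. Add a sensitivity analysis that moves plain groceries from convenience stores and bakeries (for example milk or loaf bread) to Home by food code.
4. Optionally, add a code for ready-to-eat supermarket food for future records. If this is done, date the change and keep the narrower outcome for earlier records.

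Steps 1 to 3 cost some rewording, a list of food codes and one extra column of results. Step 4 costs a change to the pick-list and leaves two versions of the source variable within one sample.
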